for COVID-19 relevant preconditions: cardiovascular diseases, diabetes, hypertension, serious heart, lung or renal diseases, immunosuppressing conditions or medication and any form of active cancer. Furthermore, participants (staff and residents) will be asked if they received a COVID-19 vaccination (date, type of vaccine, number of doses), underwent a PCR-/ antigen-test, the date of this test and the result (if more than one test was performed, the date of the first positive test has to be given) or if COVID-19 was confirmed by a CT-scan, and, if they experienced COVID-19 symptoms and when (date). The COVID-19 symptoms episode will be defined according to the Sciensano case definition:

- At least one of following acute principal symptoms not explained by another clear cause: coughing, dyspnoea, chest pain, sudden loss of olfactory sense and/or taste;

OR

- At least two of following symptoms not explained by another clear cause: fever, myalgia, tiredness, rhinitis symptoms, sore throat, head ache, anorexia, diarrhoea, acute confusion, sudden collapse

OR

- Worsening of chronic respiratory symptoms (COPD, asthma, chronic cough) not explained by another clear cause

Additionally, staff members are asked questions concerning vaccine hesitancy (if and why they hesitated to get vaccinated against COVID-19), see Appendix 6.3.

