#### **3.2 Statistical analysis**

##### **Primary objectives**

1. To assess the seroprevalence of SARS-CoV-2 among NH residents and staff in Belgium at month 0 and at every follow-up visit in the cohort at month 2, 4, 6, 8 and 10.

The seroprevalence of SARS-CoV-2 among NH residents and staff in Belgium at month 0, and follow-up in the cohort at month 2, month 4, month 6, month 8 and month 10, will be reported stratified for staff and residents, as well as a total seroprevalence with the 95% confidence interval (CI), assessed by a generalized equation estimation (GEE) analysis with independence covariance structure. The average seroprevalence in Belgian NH will be estimated via a generalized equation estimation (GEE) analysis with exchangeable covariance structure. All characteristics will also be displayed for the Belgian regions separately.

2. To assess the sero-incidence of SARS-CoV-2 among NH residents and staff in Belgium over five two month time frames and summarised over a ten month time period.

The sero-incidence of SARS-CoV-2 among NH residents and staff in Belgium over 5 two month time periods, as well as summarized over a period of 10 months, will be estimated as a total sero-incidence, as well as for NH residents staff separately, via a clustered Poisson (or binomial) regression, taking the clustered nature of participants within nursing homes into account.

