10. Indien van toepassing, bent u gevaccineerd met een vaccin tegen COVID-19?  
 Zo ja, datum van de uw vaccinatie. (*Deze vraag zal ingevoerd worden zodra van toepassing*)

***Vaccine hesitancy bij medewerkers van woonzorgcentra in België: éénmalige vragenlijst als onderdeel van de follow-up vragenlijst***

A . Bent u reeds gevaccineerd tegen COVID-19?

- Ja, ik ben reeds gevaccineerd (1 of 2 dosissen)
  - Heeft u getwijfeld voor u hebt besloten zich te laten vaccineren? Ja/nee
    - Indien ja → vraag B + C
    - Indien nee → einde vragenlijst
- Ik word binnenkort gevaccineerd
  - Heeft u getwijfeld om zich te laten vaccineren? Ja/nee
    - Indien ja → vraag B + C
    - Indien nee → vraag D
- Ik twijfel of ik me zou laten vaccineren
  - Vraag B
- Ik heb besloten om me niet te laten vaccineren
  - Vraag E

B . Wat is de hoofreden waarom u twijfelt/twijfelde om gevaccineerd te worden tegen COVID-19?

- Ik ben/was bezorgd over onbekende toekomstige effecten van het vaccin
- Ik ben/was bezorgd over de bijwerkingen van het vaccin
- Ik vertrouw/vertrouwde vaccinaties niet.
- Ik heb/had het idee dat het onwaarschijnlijk is dat ik ernstig ziek zal worden van het coronavirus
- Ik vind/vond dat de impact van het coronavirus wordt overdreven
- Ik denk/dacht dat het vaccin niet kan verhinderen dat ik besmet zal geraken met het virus
- Ik heb een aandoening waardoor het vaccin niet veilig is voor mij
- Ik ben reeds besmet geweest met COVID-19 dus ik heb geen vaccin nodig
- Ik ben bang van naalden
- Ik heb geen mensen in mijn omgeving die tot de risicogroep behoren
- Anders : \_\_\_\_\_ (deelnemers krijgen een invulveld)
- Ik verkies niet te antwoorden

C. Wat is de hoofreden waarom u besloot u toch te laten vaccineren?

- Ik vond de resultaten van de eerste vaccinaties geruststellend
- Ik had meer tijd nodig om me te informeren
- Een vriend/ familielid/ gezondheidsprofessional heeft het mij aanbevolen
- Iemand uit mijn omgeving werd ernstig ziek van het coronavirus
- Ik voelde de nood om te laten vaccineren om andere kwetsbare mensen te beschermen tegen het virus
- Ik ben bang dat ik zonder vaccinatie niet meer zal kunnen reizen
- Ik denk dat het vaccin deze gezondheidscrisis zal oplossen
- Ik voelde me onder druk gezet door mijn professionele omgeving
- Ik voelde me onder druk gezet door familieleden/vrienden
- Ik volgde de overheidsaanbeveling om me te laten vaccineren (veiligheidsraad, sensibilisering affiches, etc.)

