  - En dehors du WZC
  - La source de la contamination m'était inconnue
17. Avez-vous ressenti un ou plusieurs des symptômes suivants pendant une période comprise entre février 2020 et maintenant, sans aucune explication claire à ce sujet? Indiquez ce qui s'applique (options de réponses multiples).
- Toux
  - Essoufflement
  - Douleur thoracique
  - Perte de goût
  - Perte d'odeur
  - Aggravation des maladies respiratoires chroniques (ex: BPCO, asthme, toux chronique, ...)
  - Fièvre
  - fatigue musculaire
  - Fatigue
  - Nez qui coule / bouché
  - Gorge irritée
  - Mal de crâne
  - Perte d'appétit
  - La diarrhée
  - Confusion aiguë
  - Chute soudaine
18. Si oui, quand avez-vous ressenti ces symptômes? Veuillez indiquer le jour approximatif où ces symptômes ont commencé.

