28. Le cas échéant, avez-vous été vacciné avec un vaccin COVID-19?

Dans l'affirmative, date de votre vaccination. (Cette question sera saisie dès que applicable)

**Hésitation vaccinale au sein du personnel de soin des maisons de repos belges: questions additionnelles incluent une seule fois dans le questionnaire de suivi**

A . Êtes-vous vacciné contre la Covid-19 ?

- Je suis déjà vacciné(e) (1 ou 2 doses).
  - Avez-vous hésité avant d'être vacciné(e) ? Oui/non
    - *Si oui* → *question B + C*
    - *Si non* → *fin de questionnaire*
- Je serai vacciné(e) prochainement.
  - Avez-vous hésité à vous faire vacciner ? Oui/non
    - *Si oui* → *question B + C*
    - *Si non* → *question D*
- J'hésite à être vacciné(e).
  - *Si oui* → *Question B*
- J'ai décidé de ne pas me faire vacciner.
  - *Si oui* → *Question E*

B . Quelle est la raison principale pour laquelle vous avez hésité à être vacciné contre la Covid-19 ?

- J'étais inquiet(e) à propos d'effets secondaires futurs inconnus.
- J'étais inquiet(e) des effets secondaires.
- Je n'avais pas confiance en la vaccination.
- J'avais l'impression d'avoir peu de chances d'être gravement malade à cause du coronavirus.
- Je pensais que l'impact du coronavirus est grandement exagéré.
- Je ne pensais pas que ça m'empêcherait d'attraper le coronavirus.
- Je présente une maladie qui rendrait le vaccin dangereux pour moi.
- J'ai déjà contracté le coronavirus donc je n'ai pas besoin du vaccin.
- J'ai peur des aiguilles.
- Je ne côtoie pas de personne à risque.
- Autre : \_\_\_\_\_(les participants peuvent donner une proposition)
- Je préfère ne pas répondre.

C . Quelle est la raison principale qui vous a fait changer d'avis à propos de la vaccination ?

- Je pense que les données des premières vaccinations étaient rassurantes.
- J'avais besoin de plus de temps pour m'informer.
- Un ami/membre de la famille/professionnel de la santé me l'a recommandé.
- J'ai été confronté(e) à une personne atteinte sévèrement du coronavirus.
- Un pourcentage de plus en plus grand de la population belge a accepté d'être vacciné.
- Je ressens le besoin de me faire vacciner pour protéger les personnes vulnérables.
- J'ai peur qu'une mesure m'interdise de voyager en n'ayant pas été vacciné(e).
- Je pense que le vaccin permettra de mettre fin à la crise sanitaire/économique.
- J'ai été soumis(e) à la pression d'un supérieur.
- J'ai été soumis(e) à la pression de mes proches.

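### The French questionnaires ask about muscle fatigue where the protocol's symptom-episode definition and the Dutch forms ask about muscle pain, and two staff vaccine-hesitancy questions differ by language

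*Protocol*

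**What the plan says.** Section 2.7.2 gives three routes to a symptom episode. The first begins "At least one of following acute principal symptoms not explained by another clear cause". The second begins "At least two of following symptoms not explained by another clear cause: fever, myalgia, tiredness" and continues through seven further minor symptoms. The third is worsening of chronic respiratory symptoms. Myalgia and tiredness are separate entries in the second list.

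Appendix 6.3 holds the questionnaires in Dutch and French. Each language has four individual forms: baseline and follow-up, for staff and for residents. In the position of myalgia, all four Dutch forms have *Spierpijn* (muscle pain). All four French forms have "fatigue musculaire" (muscle fatigue), and the next line is a separate item for fatigue.

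The staff follow-up form also carries the one-off hesitancy module.

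- **Question B, Dutch:** "Wat is de hoofreden waarom u twijfelt/twijfelde om gevaccineerd te worden tegen COVID-19", which covers present and past hesitation.
- **Question B, French:** "Quelle est la raison principale pour laquelle vous avez hésité à être vacciné contre la Covid-19", past only. In both languages, staff who are still hesitating are routed to B.
- **Question C (main reason for being vaccinated after all):** the French list includes "Un pourcentage de plus en plus grand de la population belge a accepté d'être vacciné". The Dutch list has no counterpart.
- **Question C, pressure at work:** the Dutch option is "Ik voelde me onder druk gezet door mijn professionele omgeving", that is, pressure from the professional environment. The French option names pressure from a superior only.

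**The concern.** A translated form should measure what the protocol defines, and on the muscle item the French form does not. A French-language respondent who is only tired may tick both fatigue-type items and reach two minor symptoms on one complaint. A respondent with muscle pain and one other minor symptom has no box for the muscle pain and may fall short of two. The Dutch forms carry neither error.

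Symptoms bear on the goal stated in section 1, to learn about asymptomatic cases and to relate seropositivity to clinical manifestation. The hesitancy reasons are an aim of the amendment, which added the module after 15% of sampled staff were found to be unvaccinated. Question C asks for a single main reason, so the options offered help to shape the distribution of answers. If either set of data is later compared between Dutch and French forms, part of any difference could come from the form.

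**Working it through.** **Step 1: symptom lists side by side.** Each form lists 16 items: 5 principal symptoms, 1 item on chronic respiratory worsening and 10 minor symptoms (5 + 1 + 10 = 16). Fifteen of the 16 correspond between languages. The exception is the muscle item:

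| Form | Dutch item | French item |
|---|---|---|
| Baseline, staff | Q12: muscle pain | Q17: muscle fatigue |
| Baseline, residents | Q13: muscle pain | Q26: muscle fatigue |
| Follow-up, staff | Q8: muscle pain | Q26: muscle fatigue |
| Follow-up, residents | Q9: muscle pain | Q19: muscle fatigue |

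The same word recurs on all four French forms, so it is not an artefact of text extraction. The Dutch wording agrees with section 2.7.2.

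**Step 2: when the muscle item decides case status.** Under section 2.7.2 a person is a case with any principal symptom, or with chronic respiratory worsening, or with at least two minor symptoms. The other 15 items give 2^15 = 32,768 tick patterns. Switching the muscle item on or off changes case status in 9 of them: no principal symptom, no chronic worsening, and exactly one of the other nine minor symptoms. Patterns are not equally likely, so 9 in 32,768 is not a rate. It shows only that there is a single route to misclassification.

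**Step 3: an illustration, not an estimate.** The documents give no symptom frequencies. Assume, purely to see the mechanism, that all items are independent with the same prevalence q. The probability that the muscle item is decisive is then

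p = (1 − q)^6 × 9q(1 − q)^8 = 9q(1 − q)^14.

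If the prevalence of the muscle item also differed between languages by q itself, the share classed as an episode would shift by p × q:

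| q | p | p × q |
|---|---|---|
| 0.02 | 0.1357 | 0.0027 |
| 0.05 | 0.2195 | 0.0110 |
| 0.10 | 0.2059 | 0.0206 |
| 0.20 | 0.0792 | 0.0158 |

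Under these assumptions the shift is about 0.3 to 2.1 percentage points. Independence understates the chance that a tired person ticks both French fatigue items. Missed muscle pain works in the other direction. Neither the net sign nor the size can be taken from the documents.

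**Step 4: the hesitancy module.** Option counts, including the free-text and prefer-not-to-answer options:

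| Question | Dutch | French |
|---|---|---|
| B | 12 | 12 |
| C | 15 | 16 |
| D | 7 | 7 |
| E | 12 | 12 |

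Without those two options, C has 15 − 2 = 13 reasons in Dutch and 16 − 2 = 14 in French. The extra French reason is the growing share of the population accepting vaccination. The workplace-pressure option is narrower in French. The options of B match in content, so its difference is one of tense.

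**Step 5: what uses these data.** Section 3.2 has no analysis of symptom episodes or of hesitancy reasons. Infection events in its survival analyses are defined by PCR, antigen test, CT scan or saliva test.

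**The case against.** The strongest reply is that nothing in the analysis plan turns on these items. That stands: the objectives in section 2.1 include neither an asymptomatic share nor clinical manifestation, and section 3.2 analyses neither symptoms nor hesitancy reasons.

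A reader might infer from "All characteristics will also be displayed for the Belgian regions separately" that regional comparisons of symptoms and hesitancy are planned. The documents do not support this. The sentence closes the seroprevalence paragraph under primary objective 1 and mentions neither.

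Other limits also stand:

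- The symptom question asks only for symptoms without a clear explanation, which should reduce reports of ordinary tiredness.
- Resident forms (1,656 of 3,036 participants, 54.5%) are completed by trained study staff, so careless self-ticking is not the route there.
- Question C has a free-text option in both languages, through which a Dutch-form respondent could give the missing reason.
- In French question B several options are in the present tense and routing from current hesitation is explicit, so most respondents would understand it.

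These points limit the consequence but do not remove the discrepancy. The French word departs from the protocol's own definition on every individual form, including those completed by study staff. A free-text field is not equivalent to a listed option when one main reason is requested.

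**Conclusion.** The French forms, as written, do not measure one component of the protocol's symptom-episode definition, and they count fatigue-type complaints twice. Misclassification by form language is possible in either direction, but only through the two-minor-symptom rule. Hesitancy question C offers different choices in the two languages, and question B has a stem that does not fit staff who are still hesitating. This is a minor measurement point with no bearing on the primary, secondary or tertiary analyses in section 3.2.

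Two stronger readings are tempting. One is that symptom episodes and hesitancy reasons cannot be compared between languages at all. The documents do not support that: 15 of 16 symptom items correspond, B has matching options, and D and E agree.

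The other is a specific error rate. If 10–20% of French-form respondents had tiredness alone and half of them ticked both items, 5–10% would be misclassified (0.10 × 0.5 to 0.20 × 0.5). Nothing in the documents supports either input, and the product leaves out the cases missed for want of a muscle-pain box.

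**What to change.** Replace "fatigue musculaire" with *douleurs musculaires* on all four French individual forms. Give hesitancy question C the same option list in both languages, including the reason now found only in French and one common wording for pressure at work. Put the French stem of question B in present and past, as in Dutch.

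For rounds already collected, if symptom episodes are reported or compared by language or region, add a sensitivity analysis that leaves the muscle item out of the definition in both languages.

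The cost is a text change in the online questionnaire and an ethics notification. The drawback is a break in the French muscle item, which will not be directly comparable before and after the correction.

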### **Version pour les résidents participants**

*(à remplir par le chercheur; à demander par l'infirmière (chef) ou le représentant du résident)*

15. Veuillez saisir le numéro d'étudiant unique du participant. (liste cfr avec nombres aléatoires et numéros d'étude, retournée par le centre de recherche UGent)
16. Veuillez entrer l'âge du participant.
17. Quel est le sexe du participant? H / F
18. À quelle catégorie de soins appartient le résident?

O:     A:     B:     Cc:     CD:     RÉ:

19. Le participant séjourne-t-il dans un service pour résidents atteints de démence?

20. • Le participant a-t-il été vacciné contre le COVID-19?

- Oui, une dose
- Oui, deux doses
- Non

o Si oui, quel vaccin le participant a-t-il reçu

☐ Le vaccin AstraZeneca / Oxford

☐ Le vaccin BioNtech-Pfizer

☐ Le vaccin Moderna

o Si oui, date de vaccination (première seringue).

21. Le participant souffre-t-il de l'une des conditions suivantes? Indiquez ce qui s'applique (options de réponses multiples).

- Maladie cardiaque et vasculaire
- Diabète
- Hypertension artérielle (hypertension)
- Maladie pulmonaire / cardiaque / rénale sévère
- Système immunitaire affaibli (troubles immunosuppresseurs) ou système immunitaire affaibli par l'utilisation à long terme de médicaments immunosuppresseurs (ex: chimiothérapie, patients transplantés, rhumatismes immunosuppresseurs, ...)
- Maladie cancéreuse active
- Aucune de ces réponses

22. Le participant a-t-il déjà été testé pour le coronavirus (via PCR / test rapide AG / ou radiologiquement via CT scan)? Oui Non

23. Si c'est le cas. Le participant a-t-il déjà été testé positif pour le coronavirus?

- Oui, via un test PCR (test dans lequel un échantillon est prélevé via un écouvillon nasal et vous obtenez le résultat après analyse en laboratoire)
- Oui, via un test rapide d'antigène (test dans lequel un échantillon est prélevé via un tampon nasal et le résultat peut être lu en 15 minutes)
- Oui, radiologiquement, via un scanner
- Non

24. Si oui, date du 1er test PCR positif ou test rapide (approximative)?

25. Si le COVID-19 a été confirmé radiologiquement par un scanner, indiquez la date de ce scanner.

26. Le participant a-t-il ressenti un ou plusieurs des symptômes suivants pendant une période comprise entre février 2020 et maintenant, sans explication claire à ce sujet? Indiquez ce qui s'applique (options de réponses multiples).

- Toux

- Essoufflement
- Douleur thoracique
- Perte de goût
- Perte d'odeur
- Aggravation des maladies respiratoires chroniques (ex: BPCO, asthme, toux chronique, ...)
- Fièvre
- fatigue musculaire
- Fatigue
- Nez qui coule / bouché
- Gorge irritée
- Mal de crâne
- Perte d'appétit
- La diarrhée
- Confusion aiguë
- Chute soudaine

27. Si oui, quand le participant a-t-il ressenti ces symptômes? Veuillez indiquer le jour où ces symptômes ont commencé.

## QUESTIONNAIRE DE SUIVI

### Questionnaire sur les foyers de soins résidentiels (à compléter tous les 2 mois dans la semaine où le test est administré)

1. Numéro de référence de l'étude du centre d'hébergement.

Les questions 2, 3, 4 ne sont ajoutées que si non dans le questionnaire précédent.

2. Une campagne de vaccination COVID a-t-elle déjà eu lieu au WZC?

3. . Date

a. 1er tour / 2ème tour (date)

b. Quel vaccin?

i. Le Vaccin AstraZeneca / Oxford

ii. Le vaccin BioNtech-Pfizer

iii. Le vaccin Moderna

iv. Autres

4. . Combien de résidents ont été vaccinés (par rapport au nombre total de résidents?)

. Combien d'employés ont été vaccinés (par rapport au nombre total d'employés?)

5.

6. Avez-vous eu des résidents / employés testés pour COVID-19 au cours des 2 derniers mois (entre le tour de test précédent et maintenant)?

7. Si c'est le cas,
  - Via le test PCR, combien?
  - Par le biais de tests antigéniques rapides, combien?
8. Si oui, qui vous a testé? Indiquez ce qui s'applique.
  - Résidents / employés présentant des symptômes
  - Un département / corridor (préventif, par exemple après contact avec le risque)
  - Tous les résidents / employés
  - Employés seulement
  - Résidents seulement
  - Autres combinaisons?: (Champ de texte ouvert)
9. Si oui, combien de résidents / employés ont été testés positifs?
 

Pour le test PCR:

Pour le test rapide:
10. Combien de résidents sont décédés du COVID-19 au cours des 2 derniers mois?
  - Nombre de décès COVID-19 confirmés
  - Nombre de décès suspects de COVID-19

### Questionnaire individuel

(à compléter tous les 2 mois dans la semaine où le test est administré)

#### **Version pour les employés participants:**

18. Veuillez saisir votre numéro d'étudiant unique.
19. Participez-vous toujours à l'étude (ce questionnaire sera-t-il rempli)?

Sinon, pourquoi pas?

*À compléter par le chercheur*

- c. Absence provisoire de l'étude (maladie, vacances, hospitalisation ...)
- d. Le participant ne souhaite plus participer
- a. Mort suspectée ou prouvée de COVID-19 Date de décès:
- b. Décès non liés au COVID-19 Date de décès:
- c. L'employé ne travaille plus au WZC

*La question 20 n'est ajoutée que si la réponse était non auparavant.*

20. Avez-vous été vacciné contre le COVID-19?

- Oui, une dose
- Oui, deux doses
- Non

- o Si oui, quel vaccin vous a-t-il administré
    - ☐ Le vaccin AstraZeneca / Oxford
    - ☐ Le vaccin BioNtech-Pfizer
    - ☐ Le vaccin Moderna
    - ☐ autre
  - o Si oui, date de vaccination (première seringue).
- 21.
22. Avez-vous été testé pour le coronavirus (via PCR / test rapide AG / ou radiologique via CT scan) au cours des deux derniers mois? Oui Non
23. Si c'est le cas. Avez-vous été testé positif au cours des 2 derniers mois (entre le cycle de test précédent et maintenant)? Plusieurs options de réponse
- Oui, via un test PCR (test dans lequel un échantillon est prélevé via un écouvillon nasal et vous obtenez le résultat après analyse en laboratoire)
  - Oui, via un test rapide d'antigène (test dans lequel un échantillon est prélevé via un tampon nasal et le résultat peut être lu en 15 minutes)
  - Oui radiologiquement, via un scanner
  - non
24. Si oui, date du 1er test PCR positif ou test rapide au cours des 2 derniers mois (approximative)?
25. Si le COVID-19 a été confirmé radiologiquement par un scanner, indiquez la date de ce scanner.
26. Au cours des 2 derniers mois (entre la précédente série de tests et maintenant), avez-vous ressenti un ou plusieurs des symptômes suivants pendant une période, sans aucune explication claire? Indiquez ce qui s'applique (options de réponses multiples).
- Toux
  - Essoufflement
  - Douleur thoracique
  - Perte de goût
  - Perte d'odeur
  - Aggravation des maladies respiratoires chroniques (ex: BPCO, asthme, toux chronique, ...)
  - Fièvre
  - fatigue musculaire
  - Fatigue
  - Nez qui coule / bouché
  - Gorge irritée
  - Mal de crâne
  - Perte d'appétit
  - La diarrhée
  - Confusion aiguë
  - Chute soudaine

27. Si oui, quand avez-vous ressenti ces symptômes? Veuillez indiquer le jour où ces symptômes ont commencé.

28. Le cas échéant, avez-vous été vacciné avec un vaccin COVID-19?

Dans l'affirmative, date de votre vaccination. (Cette question sera saisie dès que applicable)

**Hésitation vaccinale au sein du personnel de soin des maisons de repos belges: questions additionnelles incluent une seule fois dans le questionnaire de suivi**

A . Êtes-vous vacciné contre la Covid-19 ?

- Je suis déjà vacciné(e) (1 ou 2 doses).
  - Avez-vous hésité avant d'être vacciné(e) ? Oui/non
    - *Si oui* → *question B + C*
    - *Si non* → *fin de questionnaire*
- Je serai vacciné(e) prochainement.
  - Avez-vous hésité à vous faire vacciner ? Oui/non
    - *Si oui* → *question B + C*
    - *Si non* → *question D*
- J'hésite à être vacciné(e).
  - *Si oui* → *Question B*
- J'ai décidé de ne pas me faire vacciner.
  - *Si oui* → *Question E*

B . Quelle est la raison principale pour laquelle vous avez hésité à être vacciné contre la Covid-19 ?

- J'étais inquiet(e) à propos d'effets secondaires futurs inconnus.
- J'étais inquiet(e) des effets secondaires.
- Je n'avais pas confiance en la vaccination.
- J'avais l'impression d'avoir peu de chances d'être gravement malade à cause du coronavirus.
- Je pensais que l'impact du coronavirus est grandement exagéré.
- Je ne pensais pas que ça m'empêcherait d'attraper le coronavirus.
- Je présente une maladie qui rendrait le vaccin dangereux pour moi.
- J'ai déjà contracté le coronavirus donc je n'ai pas besoin du vaccin.
- J'ai peur des aiguilles.
- Je ne côtoie pas de personne à risque.
- Autre : \_\_\_\_\_(les participants peuvent donner une proposition)
- Je préfère ne pas répondre.

C . Quelle est la raison principale qui vous a fait changer d'avis à propos de la vaccination ?

- Je pense que les données des premières vaccinations étaient rassurantes.
- J'avais besoin de plus de temps pour m'informer.
- Un ami/membre de la famille/professionnel de la santé me l'a recommandé.
- J'ai été confronté(e) à une personne atteinte sévèrement du coronavirus.
- Un pourcentage de plus en plus grand de la population belge a accepté d'être vacciné.
- Je ressens le besoin de me faire vacciner pour protéger les personnes vulnérables.
- J'ai peur qu'une mesure m'interdise de voyager en n'ayant pas été vacciné(e).
- Je pense que le vaccin permettra de mettre fin à la crise sanitaire/économique.
- J'ai été soumis(e) à la pression d'un supérieur.
- J'ai été soumis(e) à la pression de mes proches.
- J'ai suivi les recommandations gouvernementales (conseils nationaux de sécurité, spots publicitaires, ...).
- Je suis devenu(e) une personne à risque durant la crise.
- J'ai été informé(e) que j'étais une personne à risque de contracter une forme sévère du virus.
- J'ai été sensible à l'apparition de nouveaux variants du coronavirus plus contagieux.
- Autre : \_\_\_\_\_ (*les participants peuvent donner une proposition*)
- Je préfère ne pas répondre

D . Quelle est la/les raison(s) du délai de vaccination ? (*les participants peuvent cocher plusieurs cases*)

- J'étais absent(e) du travail (vacances ou maladie) lors de la première vague de vaccination et je n'ai pas eu l'opportunité d'être vacciné(e) depuis.
- J'ai une maladie chronique et la vaccination ne m'était pas recommandée au moment de la première vague de vaccination.
- J'étais enceinte et la vaccination ne m'était pas recommandée au moment de la première vague de vaccination.
- J'envisage d'être enceinte prochainement.
- J'attendais un vaccin spécifique.
- Autre : \_\_\_\_\_ (*les participants peuvent donner une proposition*)
- Je préfère ne pas répondre.

E. Quelle est la raison principale pour laquelle vous ne voulez pas être vacciné(e) contre le coronavirus ?

- Je suis inquiet(e) à propos d'effets secondaires futurs inconnus.
- Je suis inquiet(e) des effets secondaires.
- Je n'ai pas confiance en la vaccination.
- J'ai l'impression d'avoir peu de chances d'être gravement malade à cause du coronavirus.
- Je pense que l'impact du coronavirus est grandement exagéré.
- Je ne pense pas que ça va m'empêcher d'attraper le coronavirus.
- Je présente une maladie qui rendrait le vaccin dangereux pour moi.

- J'ai déjà contracté le coronavirus donc je n'ai pas besoin du vaccin.
- J'ai peur des aiguilles.
- Je ne côtoie pas de personne à risque.
- Autre : \_\_\_\_\_ (*les participants peuvent donner une proposition*)
- Je préfère ne pas répondre.

